**Methods: Monitoring**			
Data monitoring committee	28a	Composition of data monitoring committee (DMC); summary of its role and reporting structure; statement of whether it is independent from the sponsor and funder; conflicts of interest and reference to where further details about its charter can be found, if not in the protocol. Alternatively, an explanation of why a DMC is not needed	NA
	28b	Explanation of any interim analyses and stopping guidelines, including who will have access to these interim results and make the final decision to terminate the trial	NA
Trial monitoring	29	Frequency and procedures for monitoring trial conduct. If there is no monitoring, give explanation	11-12
**Ethics**			
Research ethics approval	30	Plans for seeking research ethics committee/institutional review board approval	5
Protocol amendments	31	Plans for communicating important protocol modifications to relevant parties	NA
Consent or assent	32a	Who will obtain informed consent or assent from potential trial participants or authorized proxies, and how	6
	32b	Additional consent provisions for collection and use of participant data and biological specimens in ancillary studies, if applicable	NA
Confidentiality	33	How personal information about potential and enrolled participants will be collected, shared, and maintained in order to protect confidentiality before, during, and after the trial	6
Ancillary and post-trial care	34	Provisions, if any, for ancillary and post-trial care, and for compensation to those who suffer harm from trial participation	NA

Citation: Chan A-W, Boutron I, Hopewell S, Moher D, Schulz KF et al. SPIRIT 2025 statement: updated guideline for protocols of randomised trials. BMJ 2025; 389:e081477. https://dx.doi.org/10.1136/bmj-2024-081477.

© 2025 Chan A-W et al. This is an Open Access article distributed under the terms of the Creative Commons Attribution License (https://creativecommons.org/licenses/by/4.0/), which permits unrestricted use, distribution, and reproduction in any medium, provided the original work is properly cited.

a We strongly recommend reading this checklist in conjunction with the SPIRIT 2025 Explanation and Elaboration and the SPIRIT 2025 Expanded Checklist for important clarifications on all the items. We also recommend reading relevant SPIRIT extensions. See www.consort-spirit.org.

#### Approach to managing missing data

3.12.2

We will evaluate baseline characteristics across study groups to determine if randomization effectively balances covariates. All outcome analyses will follow an intent-to-treat approach. Participant dropout will be closely monitored to assess whether the missing data is informative. Additionally, we will examine how differences in dropout rates between groups may influence the primary and secondary outcomes.

#### Analysis plan

3.12.3

We will report proposed outcome measures using descriptive measures. A difference and its 95% confidence interval in an outcome endpoint will be estimated via conducting pairwise comparisons between each intervention arm (***CostCOM*** or ***FinEd***) versus ***EUC*** arm. The Exact (Clopper-Pearson) method will be utilized to obtain a 95% confidence interval. Logistic regressions will be used to evaluate the impact of potential co-variates on primary endpoint among study arms. Linear regression analysis will be utilized to model a continuous outcome. For the longitudinal outcomes, we will implement the Generalized Estimating Equations (GEE) approach to adjust for the systematically different observation periods, in which time will be modeled as a fixed effect at each step**.**

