**Fig. 1 fig1:**
[figure not shown]
Study schema.

Routine screening for financial hardship and HRSNs in clinical oncology practices is limited by staffing constraints and absence of standardized screening tools [10]. While several screening tools have demonstrated feasibility and acceptability [[16], [17], [18]], and over 70% of community oncology practices report available services to screen for and respond to financial hardship and HRSNs [19], screening remains uncommon as availability of the service does not equate coverage of all patients at risk. Notably only 16.6% of cancer patients were actually screened in a retrospective analysis of a single comprehensive cancer center [10]. This gap highlights the need for approaches that reduce staff burden while addressing patient needs.

Beyond screening, responding to identified needs is also limited by staffing and lack of referral systems [18]. Interventions such as financial navigation, financial education, and cost communication have been proposed [[20], [21], [22]]. While financial navigation improved financial worry among high-risk patients [19], its implementation is constrained by the need for trained navigators. As financial hardship is associated with low financial health literacy [22] and financial self-efficacy [23], financial education may also be effective. However, prior financial education studies have also relied on delivery by navigators [23,24]. It remains unclear whether navigator-free approaches—such as self-directed educational materials and financial resources—are more effective than usual care, or how they compare to active financial navigation in improving financial hardship and quality of life. Further, financial hardship has been associated with poor sleep quality, including increased insomnia severity and sleep disturbances among cancer patients [15]. Given that financial stress is a recognized psychosocial stressor capable of activating physiological pathways that interfere with sleep, interventions targeting financial hardship may plausibly improve sleep outcomes as a secondary benefit. However, the extent to which financial hardship-focused interventions may improve sleep quality among cancer patients remains largely unexplored. Therefore, sleep quality was included as an outcome in the present pilot study to assess whether reductions in financial hardship are accompanied by improvements in this dimension of patient well-being.

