## Objectives

2

We will investigate the preliminary efficacy of FinEd vs. EUC vs. CostCOM within six months after randomization on patient-reported cost-related cancer care non-adherence (primary outcome), electronic medical record (EMR)-abstracted treatment completion, missed appointments, patient-reported financial worry, material financial hardship, health insurance literacy, QOL, and sleep quality as well as objectively measured sleep quality (secondary outcomes). We will further describe FinEd arm patient experience with the FinEd intervention using mixed methods (implementation outcome).

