## Discussion

4

Financial hardship and HRSNs are persistent, under-addressed barriers in cancer care that contribute significantly to disparities in treatment adherence, quality of life (QOL), and clinical outcomes [6,[8], [9], [10], [11], [12], [13], [14],^20^]. Despite growing recognition of their impact, scalable and sustainable solutions remain limited. Our protocol seeks to evaluate the feasibility, acceptability, and preliminary efficacy of a navigator-free intervention—FinEd—as a potentially cost-effective and scalable alternative to the previously studied CostCOM intervention, which requires trained financial navigators. We aim to compare FinEd, CostCOM, and EUC among cancer patients who screen positive for financial hardship or HRSNs across a range of patient-reported health outcomes.

This protocol introduces several key innovations that address critical gaps in cancer care related to financial hardship and HRSNs. By focusing on populations at heightened risk for financial hardship and HRSNs, and who are disproportionately affected by health disparities, this study directly targets underserved and vulnerable groups. To our knowledge, this is the first study to compare FinEd, a scalable, navigator-free model that empowers patients through education and self-advocacy with usual care as well as CostCOM, a financial navigation-based intervention. The comparison of these distinct approaches will indicate relative effectiveness and inform future large-scale efforts. Moreover, the centralized delivery of both interventions—CostCOM via remote navigators and FinEd via trained research staff—reduces variability, enhancing methodological rigor. Finally, this study is novel in assessing the impact of financial interventions on sleep quality—a frequently overlooked yet highly burdensome symptom among cancer patients. Up to 79% of cancer patients experience sleep disturbances during treatment, and cancer survivors report sleep problems at rates 11–32% higher than non-cancer controls [15]. Moreover, cancer-related financial hardship has been associated with a 1.58-fold increased risk of long-term, impairing sleep problems [15].

Our findings will yield actionable information to inform and support future interventions to reduce financial hardship and HRSNs and promote care adherence, especially when there is navigator staffing shortage.

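### Section 3.12.3 plans an estimate and interval for each intervention against EUC but none for FinEd against CostCOM, a comparison the stated aims promise

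*Protocol article*

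**What the plan says.** **The planned contrasts.** Section 3.12.3 (Analysis plan) states that an outcome difference with a 95% interval "will be estimated via conducting pairwise comparisons between each intervention arm", and then names the pairs as CostCOM or FinEd against EUC. The same section adds: "Logistic regressions will be used to evaluate the impact of potential co-variates on primary endpoint among study arms". Linear regression is planned for continuous outcomes and GEE for longitudinal ones. Neither of those sentences names a contrast between arms.

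**The stated aims.**
- Section 1 (Introduction) describes the gap as whether navigator-free approaches "are more effective than usual care, or how they compare to active financial navigation in improving financial hardship and quality of life".
- Section 2 (Objectives): "We will investigate the preliminary efficacy of FinEd vs. EUC vs. CostCOM within six months after randomization".
- The Abstract's conclusion and the last paragraph of the Introduction use the same three-way framing.
- Section 4 (Discussion) presents FinEd as a possible alternative to CostCOM and says: "The comparison of these distinct approaches will indicate relative effectiveness and inform future large-scale efforts".

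**Design.** Section 3.6 randomizes 1:1:1 in blocks of 3, and Section 3.12.1 sets 30 patients per arm.

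**The concern.** The Introduction poses two questions: FinEd against usual care, and FinEd against navigation. The first has a planned difference and interval. The second has neither, yet the Discussion says the trial will speak to it.

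A reader who wants the second answer would have to compare the CostCOM–EUC result with the FinEd–EUC result by eye. If one interval excludes 0 and the other does not, the natural reading is that one intervention works and the other does not. If both fall on the same side, the natural reading is that FinEd does as well as CostCOM. Neither conclusion follows. The second would be attractive here, because the rationale for FinEd is a shortage of navigators. Choosing the contrast only after results are known would also be weaker than naming it now.

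**Working it through.** **1. Aims against planned contrasts.** Three arms give three pairs.

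| Pair | Promised in the aims | Difference and 95% CI named in 3.12.3 |
|---|---|---|
| CostCOM – EUC | yes | yes |
| FinEd – EUC | yes | yes |
| FinEd – CostCOM | yes (Introduction, Objectives, Discussion) | no |

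The regression and GEE sentences do not fill the gap. The logistic model is described as serving the effect of covariates, and the other two name no pair.

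**2. The plan's own figures.** Table 2 gives one-sided Clopper-Pearson upper limits for one arm of n = 30. With x = 30P, the limit is the Beta(x + 1, 30 − x) quantile at the stated confidence. At 95% this gives 0.17251, 0.2386 and 0.29948 for P = 0.05, 0.10 and 0.15. All nine entries reproduce. They describe the proportion in a single arm and say nothing about any difference between arms.

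**3. Precision of the missing contrast.** The documents give no FinEd or CostCOM rates, so I assume equal rates across the Table 2 range, with n = 30 per arm.

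- Newcombe: for equal rates p with Wilson 95% limits (l, u), half-width = √[(p − l)² + (u − p)²].
- Wald: half-width = 1.96 × √[2p(1 − p)/30].

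| Assumed rate in both arms | Wilson limits | Newcombe half-width | Wald half-width |
|---|---|---|---|
| 0.05 | 0.012 to 0.191 | 0.146 | 0.110 |
| 0.10 | 0.035 to 0.256 | 0.169 | 0.152 |
| 0.15 | 0.063 to 0.316 | 0.188 | 0.181 |

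Example at 0.10, with limits to four places: √[(0.10 − 0.0346)² + (0.2562 − 0.10)²] = √(0.0043 + 0.0244) = 0.169.

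With unequal assumed rates of 0.15 and 0.05, the Newcombe interval is −0.065 to 0.271. Power at two-sided 0.05 is about 25%, and 80% power would need 141 per arm. For 0.10 and 0.05, power is about 11% and 435 per arm would be needed. The contrast can be estimated but cannot be tested usefully.

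**4. Why two results against EUC do not replace it.** The two contrasts share the EUC arm, and EUC cancels from their difference: (FinEd − EUC) − (CostCOM − EUC) = FinEd − CostCOM. Treating them as independent counts the EUC variance twice. At a rate of 0.10 the Wald half-width rises from 1.96 × √(2 × 0.09/30) = 0.152 to 1.96 × √(4 × 0.09/30) = 0.215.

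**5. Illustration of the misreading.** The counts are assumed and are not from the documents: EUC 8/30, CostCOM 2/30, FinEd 4/30. Newcombe 95% intervals:

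- CostCOM − EUC: −0.200 (−0.384 to −0.007)
- FinEd − EUC: −0.133 (−0.328 to 0.072)
- FinEd − CostCOM: +0.067 (−0.100 to 0.237)

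The planned output would show the first two lines, of which only one excludes 0. The third line shows that these data do not separate the two interventions.

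**The case against.** **The source is a condensed article and no SAP is shown.** A full list of model contrasts often sits in the SAP, and naming two comparisons does not expressly exclude a third. This has some force, and an unseen SAP may contain the contrast. But the article is not silent here. It lists its between-arm differences, and that list does not match its own aims. If the SAP does add the contrast, Section 3.12.3 still needs to be brought into line.

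**The models could supply it.** A three-arm logistic, linear or GEE fit yields FinEd versus CostCOM directly, and nothing restricts those models to EUC. That is true, and it makes the fix easy. It does not amount to planning the contrast.

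**This is a pilot.** No test or decision rule rests on the comparison, power is low, the aims are repeatedly called preliminary or initial, and no equivalence claim is planned. All of this stands and limits the seriousness. It does not justify leaving the pair out, because the two planned contrasts rest on the same 30 per arm.

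**Stronger readings that a reader might infer.** One is that the trial cannot answer the question. The documents do not support that: the arms are randomized concurrently, surveyed at the same times and analysed by intention to treat, so the gap lies in the written analysis. Another is that FinEd versus CostCOM is the single novel contrast. The Discussion claims novelty for comparing FinEd with both usual care and CostCOM.

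**Conclusion.** The point holds as an inconsistency between the aims and the analysis plan. One of the three promised pairs, FinEd against CostCOM, has no named estimate or interval in Section 3.12.3. The design is sound for it. Nothing is biased and no data are lost.

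The conclusion rests on the text alone and on no assumed rate. Its size in terms of precision is conditional: with 30 evaluable patients per arm and equal rates between 0.05 and 0.15, the 95% interval would be about ±0.15 to ±0.19 by Newcombe. An interval that wide cannot support a claim that FinEd matches CostCOM, which is a reason to show it.

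**What to change.** Make one of two changes.

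1. **Add the contrast (preferred).** In Section 3.12.3, prespecify FinEd minus CostCOM with a 95% confidence interval for the primary outcome and for the secondary outcomes that are reported against EUC. Take it from the same regression or GEE models, or use a two-sample method such as Newcombe for proportions. Clopper-Pearson is a single-proportion interval and does not itself give an interval for a difference. Label the contrast as estimation only, and state that an interval including 0 is not evidence of equivalence.
2. **Narrow the aims.** Limit the Abstract's conclusion, the Introduction, the Objectives and the relative-effectiveness statement in the Discussion to the comparisons with EUC.

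The first costs a sentence or two and one further interval per outcome. The second costs wording only. Neither needs more patients, visits or data.

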### Randomization

3.6

Consented patients who complete the baseline survey will be randomized with a 1:1:1 ratio in a block size of 3 into one of the three study arms generated using PASS 2023 [39]. Randomization will be stratified by cancer stage (1:1:1 non-metastatic vs. metastatic). Metastatic stage is defined by the presence of distant metastasis based on pathological, clinical, or lab findings, or by receipt of non-curative intent treatment. For hematologic malignancies, acute leukemias and stage IV lymphoma will be categorized under metastatic staging.

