#### Primary efficacy outcomes

3.11.1

The primary outcome is patient-reported cost-related cancer care nonadherence within 6 months post-randomization. Cost-related cancer care nonadherence is defined as a positive response to any of the following: (1) delay, (2) forego, (3) stop, or (4) change in cancer prescribed medication due to cost, (5) refuse recommended cancer tests, or (6) skip cancer office visits due to cost, adapted from Medical Expenditure Panel Survey [34]. At each of the 3-, and 6-month follow-ups, patients will be asked about the presence of nonadherence (yes/no) since the last follow-up. Cost-related cancer care nonadherence at 6 months will be calculated as a report of nonadherence at any of the 3 and 6-month follow-ups (yes/no). We will also evaluate the presence of cost-related cancer care non-adherence at each time point separately.

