#### Power calculation and sample size

3.12.1

This is a 3-arm pilot randomized controlled trial to gather preliminary data to plan for a large future trial. A sample size of 90 patients (30 patients in each arm) is feasible given the limits of the study timeline and will allow us to characterize key patient variables.

Power analysis was performed to estimate a one-sided 85%, 90% and 95% upper-limit confidence intervals for proportion of patient-reported cost-related cancer care nonadherence at 6 months post-randomization in an experimental arm via the Exact (Clopper-Pearson) formula when the evaluable sample size for a study arm is 30 (Table 2). With an evaluable sample size of 30 in an experimental arm and the anticipated proportion is 0.05, the estimated 95% upper-limit confidence limit is 0.17.

**Table 2 tbl2:** Estimation of one-sided upper-limit confidence interval for primary outcome via the Clopper-Pearson Exact method when the evaluable sample size of 30 in an experimental arm.

The proportion of patient-reported cost-related cancer care nonadherence at 6 months post-randomization in an experimental arm (P)	One-sided upper limit of a confidence interval via the Clopper-Pearson Exact method		
	85%	90%	95%
0.05	0.1296	0.14613	0.17251
0.1	0.19052	0.2093	0.2386
0.15	0.24806	0.26832	0.29948

SPIRIT 2025 checklist of items to address in a randomized trial protocol^a^			
Section/Topic	No	SPIRIT 2025 checklist item description	Reported on page no.

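### The analysis plan names a single-proportion method (Clopper-Pearson) for the 95% confidence interval of a difference between arms, so the stated method cannot give that interval for the binary outcomes

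*Protocol article*

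**What the plan says.** Section 3.12.3 (Analysis plan) of the protocol article sets the comparison: "A difference and its 95% confidence interval in an outcome endpoint will be estimated via conducting pairwise comparisons between each intervention arm", that is CostCOM or FinEd, and EUC. The sentence that follows is "The Exact (Clopper-Pearson) method will be utilized to obtain a 95% confidence interval". No other interval method is named in the section. Logistic regression is then given the task of examining co-variates for the primary endpoint, linear regression is assigned to continuous outcomes, and GEE to longitudinal ones.

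The primary outcome (section 3.11.1) is binary: any nonadherence reported at the 3- or 6-month survey. Table 1 also defines treatment completion and material hardship as yes/no.

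Section 3.12.1 uses the same method for a different purpose, to "estimate a one-sided 85%, 90% and 95% upper-limit confidence intervals for proportion of patient-reported cost-related cancer care nonadherence" in one experimental arm of 30. There it reports that when "the anticipated proportion is 0.05, the estimated 95% upper-limit confidence limit is 0.17".

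**The concern.** The only 95% interval introduced before the Clopper-Pearson sentence is the one for the between-arm difference, so the natural reading is that Clopper-Pearson is to supply it. It cannot. The method inverts a one-sample binomial test and yields limits for one proportion.

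No hypothesis test is named for the arm comparison, so the difference and its interval are the trial's main efficacy output. They are also what a larger trial would be planned from. If the stated method cannot be carried out, someone has to choose a replacement, possibly after seeing the data. With 30 patients per arm and few events, that choice can decide whether an interval includes zero.

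**Working it through.** **Inputs.** From the documents: 30 patients per arm (section 3.12.1), 1:1:1 allocation (section 3.6), a binary primary outcome (section 3.11.1), and anticipated proportions of 0.05, 0.10 and 0.15 in an experimental arm (Table 2). Assumed: all EUC rates and all event counts below, because the documents give no EUC rate.

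**Step 1. Reproduce the plan's own figures.** The one-sided Clopper-Pearson upper limit at confidence level c is the Beta quantile B(c; x + 1, n − x), with n = 30 and x = nP.

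| P | x | 85% | 90% | 95% |
|---|---|---|---|---|
| 0.05 | 1.5 | 0.1296 | 0.14613 | 0.17251 |
| 0.10 | 3.0 | 0.19052 | 0.2093 | 0.2386 |
| 0.15 | 4.5 | 0.24806 | 0.26832 | 0.29948 |

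All nine values match Table 2 to the printed digits, including the 0.17 in the text. So section 3.12.1 uses the method correctly, on one arm.

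**Step 2. What the formula can return.** Its arguments are one x and one n. A difference p1 − p2 needs x1, n1, x2 and n2, and the formula has no place for a second sample.

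**Step 3. One possible misuse, for illustration.** An analyst holding to Clopper-Pearson might take (L1 − U2, U1 − L2) from the two arms' two-sided 95% limits. For an assumed 2/30 vs 8/30 (difference −0.200):

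- Clopper-Pearson limits: 0.0082 to 0.2207 and 0.1228 to 0.4589.
- Subtracted: 0.0082 − 0.4589 = −0.451, and 0.2207 − 0.1228 = 0.098.
- Newcombe, from the Wilson limits 0.0185 to 0.2132 and 0.1418 to 0.4445. Lower: −0.200 − √[(0.0667 − 0.0185)² + (0.4445 − 0.2667)²] = −0.384. Upper: −0.200 + √[(0.2132 − 0.0667)² + (0.2667 − 0.1418)²] = −0.007.

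The subtracted interval includes zero and the Newcombe interval does not.

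**Step 4. Coverage and mean width.** These come from exact enumeration of all 31 × 31 outcomes, with 30 per arm:

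| Assumed true rates | Subtracted: coverage / width | Newcombe: coverage / width | Width ratio |
|---|---|---|---|
| 0.05 vs 0.05 | 1.000 / 0.371 | 0.993 / 0.288 | 1.29 |
| 0.05 vs 0.15 | 0.998 / 0.459 | 0.975 / 0.332 | 1.38 |
| 0.10 vs 0.10 | 0.999 / 0.472 | 0.974 / 0.334 | 1.41 |
| 0.15 vs 0.15 | 0.998 / 0.546 | 0.961 / 0.370 | 1.48 |
| 0.10 vs 0.30 | 0.997 / 0.576 | 0.955 / 0.390 | 1.48 |

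**The case against.** **The sentence may mean per-arm intervals.** It speaks of an interval without saying for what, section 3.12.3 opens with descriptive reporting, and section 3.12.1 applies the method properly to one arm. On that reading Clopper-Pearson is valid and the method for the difference is simply left unnamed, which a condensed article may do. The reading is possible but strained, because the sentence directly follows the promise of an interval for the difference. The text should rule out the other reading.

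**Continuous outcomes.** A reader might infer that Clopper-Pearson is also being imposed on financial worry, insurance literacy, quality of life and sleep scores, since the preceding sentence refers to an outcome endpoint in general. The documents do not support this. The Clopper-Pearson sentence names no endpoint type, and the same section assigns linear regression and GEE to continuous and longitudinal outcomes. Both give model-based intervals for arm contrasts.

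**The analyst is not forced into subtraction.** This objection stands. Exact unconditional intervals for a difference exist, and an analyst told to be exact might use one. For 2/30 vs 8/30 such a score interval has an upper limit of about −0.006, close to Newcombe's −0.007. The document never proposes subtracting limits, so the coverage and width figures illustrate one misuse and do not predict what the trial will report.

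**It is a pilot.** No decision threshold is tied to this interval. That limits the consequence but does not make the named method suitable.

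**Conclusion.** The point holds for the binary outcomes: as written, the method named for the between-arm interval is a one-sample method and cannot produce it. This is a wrong method stated, not a detail left to a statistical analysis plan, and it rests on reading the two adjacent sentences of section 3.12.3 together.

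The numerical consequence depends on what replaces the method. It is close to nil if a proper two-sample interval is used. It reaches 99.7-100% coverage and about 29-48% excess width if per-arm limits are subtracted, under the assumed rates and 30 evaluable patients per arm.

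A reader might go further and conclude that the trial cannot deliver a valid efficacy interval, or that its size or precision table is flawed. Neither follows. Valid intervals can be computed from the same data, Table 2 is correct, and the design and point estimates are untouched. This is a wording error in the primary comparison that should be fixed before analysis.

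**What to change.** Replace the Clopper-Pearson sentence in section 3.12.3 with text to this effect: Clopper-Pearson 95% limits describe the proportion in each arm; each pairwise risk difference versus EUC has a two-sided 95% interval by one named two-sample method; intervals for continuous and longitudinal outcomes come from the linear regression and GEE models already planned. Newcombe and Miettinen-Nurminen are both suitable for the risk difference. An exact unconditional score interval fits if the intention is to stay with exact methods.

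The cost is one sentence, with no new data or patients. The downside is minor: Newcombe coverage can fall slightly below nominal (lowest 94.2% with 30 per arm over true rates of 1-40%). If guaranteed coverage is wanted, the exact unconditional interval provides it. Whichever is chosen should be fixed before outcome data are examined, and any statistical analysis plan should carry the same wording.

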### Follow-up surveys

3.8

All patients will be surveyed at 3- and 6-months post-randomization to assess patient-reported receipt of cancer supportive services as part of usual care, cost-related cancer care nonadherence [34], material hardship [34], financial worry [31,32], QOL [35], health insurance literacy [43], subjective sleep quality [37], and patients’ experience with the CostCOM and FinEd interventions. Surveys will be distributed electronically via REDCap or by mail, with a pre-stamped, pre-addressed return envelope, according to their preferences. Non-responders of the survey will be approached to complete the survey via phone or in the clinic. Patients will be sent $30 and $40 gift cards after completion of the 3- and 6-month surveys, respectively.

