#### Secondary efficacy outcomes

3.11.2

Secondary outcomes and their definitions are shown in Table 1 and include treatment completion [47] (yes/no), rate of missed appointments [47], and material financial hardship [34] within 6 months post randomization, as well as changes in patient-reported financial worry [31,32], health insurance literacy [43], QOL [35], subjective sleep quality [37] between baseline and 3- and 6-months. A sleep quality parameters will be calculated using the Action-W program and include: sleep duration (total nighttime sleep minutes), sleep efficiency (ratio of nighttime sleep duration to total sleep period), sleep latency (minutes to first sleep epoch), and sleep fragmentation (ratio of number of nighttime awakenings to nighttime sleep duration ∗ 100). The index of sleep fragmentation considers movements of varying intensity [43].

**Table 1 tbl1:** Preliminary Efficacy Outcome Measures and co-variates.

Outcome	Definition	Source
Cost-related cancer care nonadherence *(****Primary)***	Any incidence during the 6 months (measured at 3, and 6 months) when a patient self-reports a positive response to any of: (1) delay, (2) forego, (3) stop, or (4) change in cancer prescribed medication due to cost, (5) refuse recommended cancer tests, or (6) skip cancer office visits due to cost (adapted from Medical Expenditure Panel Survey) [34]. The outcome will be binary (yes/no).	Patient surveys at 3& 6 months. Outcome will also be measured at baseline to control baseline data.
Treatment completion	Receipt of the prescribed cycle of chemotherapy and/or radiation therapy due within the 6-month study period, determined by EMR abstraction (Yes/No) [47]. Patients with treatment interruptions/stoppages because of toxicities, other medical reasons, facility factors, or death will be considered as having completed treatment if they complete all recommended treatment within the 6-month interval. Treatment interruptions/stoppages without medical reasons will be considered incomplete treatment.	EMR
Missed appointment	Proportion of outpatient medical or radiation oncology treatment appointments (including infusion) or office visits (including tele medicine) that is marked as cancellation or no shows and are provider-initiated or are not due to scheduling errors [47]	EMR

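### GEE is fixed for the longitudinal secondary outcomes with no missing-data method attached, so the plan permits an analysis that is biased if score-related dropout differs by arm

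*Protocol article*

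**What the plan says.** Section 3.12.3 (Analysis plan) assigns one method to the repeated outcomes: "For the longitudinal outcomes, we will implement the Generalized Estimating Equations (GEE) approach", to allow for differing observation periods and with time as a fixed effect. It gives no weights, imputation step or working correlation.

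Section 3.11.2 (Secondary efficacy outcomes) identifies the scores concerned: changes in financial worry, health insurance literacy, quality of life and subjective sleep quality "between baseline and 3- and 6-months". Section 3.8 sets one common schedule: "All patients will be surveyed at 3- and 6-months post-randomization".

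Section 3.12.2 (Approach to managing missing data) says "All outcome analyses will follow an intent-to-treat approach". On dropout it says "Participant dropout will be closely monitored to assess whether the missing data is informative" and "we will examine how differences in dropout rates between groups may influence the primary and secondary outcomes". It states no dropout rate and no action if either check is positive. The SPIRIT checklist marks the item on subgroup and sensitivity analyses (27d) as not applicable.

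The primary endpoint, any nonadherence reported at 3 or 6 months, is handled in section 3.12.3 by exact intervals and logistic regression.

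**The concern.** Without weighting or imputation, GEE is guaranteed consistent only when dropout is unrelated to the outcomes, given the covariates in the model. If patients with a worse 3-month score are less likely to answer at 6 months, the estimate can be biased. How far depends on the working correlation. Under independence, GEE compares the means of those still responding; a working correlation close to the truth carries information forward from earlier visits.

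Score-related dropout that differs by arm is plausible in this design, though the documents do not assert it. Participants and coordinators are unblinded. Study contact is unequal: no intervention contact in EUC, one session in FinEd, and two in CostCOM, the second at 3 months. If worried EUC patients leave more often, those remaining look better and the intervention effect is understated. That matters because the pilot's stated product is initial efficacy estimates for a larger trial. Monitoring dropout does not correct them.

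The reason given for GEE, differing observation periods, does not decide the matter, because this is a parallel trial with the same survey times for everyone.

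**Working it through.** The article gives no figure for dropout or for the longitudinal outcomes, so there is nothing on this point to reproduce. (The Table 2 limits for the primary outcome do reproduce. For example, the Beta quantile at 0.95 with parameters 1.5 + 1 = 2.5 and 30 − 1.5 = 28.5 is 0.17251.)

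**From the documents:** 30 per arm; visits at baseline, 3 and 6 months; GEE with time as a fixed effect.

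**Assumed, because the documents are silent:** SD 10; true difference 2 points at 3 months and 4 at 6 months; higher score is better; correlation 0.6 (compound symmetry) or 0.6 and 0.75 (autoregressive). Dropout at each follow-up visit, with scores measured from the control mean:

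- Unequal but random: 0.20 control, 0.06 intervention, so by 6 months 1 − 0.80² = 0.36 and 1 − 0.94² = 0.12.
- MAR, differing by arm: logit p = −1.7 − (last score)/10 in control and −2.8 in intervention. Six-month dropout is about 34% and 11%.
- MAR, same in both arms: logit p = −2.2 − (last score)/10.
- Not at random (MNAR): as the second mechanism, but driven by the current, unseen score.

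**Bias in the 6-month difference, 400,000 per arm, range over the three correlation settings.** The mixed-model column is generalised least squares with the true covariance, which flatters it slightly.

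| Dropout | GEE, independence | GEE, exchangeable or unstructured | Mixed-model stand-in |
|---|---|---|---|
| Unequal, random | −0.04 to +0.02 | −0.05 to +0.03 | −0.05 to +0.02 |
| MAR, same in both arms | −0.10 to −0.06 | −0.02 to +0.02 | −0.01 to +0.02 |
| MAR, differing by arm | −2.04 to −1.46 | −0.14 to +0.14 | −0.05 to +0.04 |
| MNAR, differing by arm | −2.71 to −2.49 | −1.68 to −1.16 | −1.64 to −1.23 |

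**At 30 per arm** (4,000 trials, MAR differing by arm, correlation 0.6): bias −1.86 with SD 2.95 for independence, −0.08 with SD 2.87 for exchangeable, −0.15 with SD 2.88 for unstructured, and +0.03 with SD 2.86 for the stand-in. In standard errors the independence bias is 1.86/2.95 = 0.63. By normal approximation a nominal 95% interval then covers Φ(1.96 − 0.63) − Φ(−1.96 − 0.63), about 90%.

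**With no true effect** (700 trials each, SD 10, correlation 0.6, 30 per arm, dropout log-odds slope 1 per SD), three cases: 30% EUC and 10% active dropout, score-driven in both arms; the same rates, score-driven in EUC only; 20% in both arms, score-driven in EUC only.

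- Independence: −1.0 / −1.6 / −1.1
- Independence with baseline as a covariate: −0.45 / −0.64 / −0.38
- Exchangeable: −0.07 / +0.11 / +0.07 (Monte Carlo error about 0.11)

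A further no-effect simulation gave −1.0 to −1.9 with 87–94% coverage for independence, and at most about 0.3 with 93–95% coverage for exchangeable. The low end is about 1.0/2.9 = 0.34 of a standard error.

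**The case against.** The strongest reply is that the bias belongs to a choice the article never makes. It does not specify independence or rule out weights or imputation, and a condensed article may leave such detail to an SAP that is not shown. Table 1 also says baseline is measured so that it can be controlled for, and baseline adjustment alone cuts the independence bias to about 35–45% of its size (0.38/1.1 to 0.64/1.6). Section 3.8 plans phone or clinic contact with non-responders and rising gift cards.

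Most of this stands, and it limits the point. The silence on working correlation is not itself an error. What remains is that the article does name the method, and its section on managing missing data contains nothing that would alter an estimate. As written, it allows both a materially biased analysis and a nearly unbiased one.

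A reader might go further and infer four things that the documents do not support:

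- That GEE is unbiased only when dropout is completely at random. Dropout depending only on arm or modelled covariates does no harm, and weighted or multiply imputed GEE is valid under MAR.
- That the plan expects informative or unequal dropout. It says only that both will be examined, and unequal rates alone gave no bias.
- That a mixed model cures informative dropout. Under MNAR its stand-in was biased by −1.2 to −1.6, much like exchangeable or unstructured GEE.
- That robust standard errors are seriously too small at 30 per arm. In the no-effect runs they were about 3–9% below the empirical SD, with 92–96% coverage, which is a minor matter.

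**Conclusion.** The point holds in a limited form. The plan fixes GEE for the longitudinal secondary scores and attaches nothing that protects the estimate if dropout depends on earlier scores differently by arm. In that case an independence working correlation costs roughly 1 to 2 points on an assumed SD-10 score, or 0.3 to 0.6 of a standard error. With an exchangeable or unstructured working correlation the bias was at most about 0.3 points in any check.

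The size rests entirely on assumed values for SD, correlation, dropout rates and the strength of score dependence. When the same score-driven mechanism acts in both arms, the bias nearly vanishes (−0.06 to −0.10).

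The consequence is modest: secondary outcomes, and possibly the by-visit nonadherence results, in a 30-per-arm pilot. The documents do not support a claim that the results will be biased, or that this GEE choice affects the primary endpoint.

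**What to change.** - **Continuous repeated scores:** use a likelihood-based mixed model for repeated measures on all observed visits, with baseline, arm, visit, arm-by-visit and stage stratum, an unstructured covariance and small-sample degrees of freedom. It is valid under MAR without leaning on a working-correlation choice. If GEE is kept, name a non-independence working correlation and a small-sample corrected variance.
- **Binary by-visit outcomes:** multiply impute before GEE.
- **Assumption:** state MAR explicitly, and add one MNAR sensitivity analysis, since neither GEE nor the mixed model corrects truly informative dropout.

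The cost is protocol and SAP wording, standard software and a little more analysis work. The one statistical downside is a normal model for bounded scores. No change to data collection or sample size is needed.
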